## Device Sterilization

The device parts that will be in contact with sterile regions in the operating room will be a standard 10-mm laparoscope, which will be sterilized according to current MSK equipment protocols. All parts will be sterilized according to the manufacturer's specifications. Other than the laparoscope, there will be no physical contact between the snap-on lens and the camera system with the patient's body. The operating personnel can operate the device and change its position during the operation, as with any handheld laparoscopic lens.

## 6.0 CRITERIA FOR PARTICIPANT ELIGIBILITY

This first-in-human study will be a phase I study of up to 50 patients with adenocarcinoma of the prostate undergoing minimally invasive radical prostatectomy. All patients enrolled in the study will undergo surgery as normally performed to current standards of care at MSK. The planned surgery and extent of dissection will not be altered based upon the fluorescent imaging of structures visualized during the case. Patients will be managed perioperatively according to existing MSK pathways developed in compliance with current recommendations and guidelines.

### 6.1 Participant Inclusion Criteria

Patients must be:

- 18 years or older and capable of signing their own consent form
- Scheduled for minimally invasive radical prostatectomy with pelvic lymph node dissection

## **6.2 Participant Exclusion Criteria**

Exclusion from the study will occur for patients with the following:

- Prior pelvic surgery or pelvic radiation therapy
- Known central nervous or peripheral nervous system disease or insult (including neurodegenerative diseases), current use of neurotoxic medications, or use of cytotoxic chemotherapy with known neurotoxicity within 1 month
- Exposure to investigational agents in the immediate 30 days before or 15 days after study drug administration
- Patients with significant renal dysfunction (<60 mL/min as assessed by the Cockcroft Gault calculation for creatinine clearance)
- Clinically significant hepatic/liver impairment (liver function tests more than 2x institutional normal upper limit)
- Exposure to phototoxic drugs such as St. John's wort, griseofulvin, thiazide diuretics, sulfonyleureas, phenothiazines, sulphonamides, quinolones, and tetracyclines, should be avoided. If safe to discontinue use for a limited time, patients may participate on this trial but will discontinue the use of the interfering drug for 5 half-lives before Illuminare-1 injection to permit full washout, as well as for 48 hours after administration of Illuminare-1.

## **7.0 RECRUITMENT PLAN**

### **7.1 Research Participant Registration**

Patients with prostate cancer scheduled to undergo surgery at MSK will be recruited from the practices of the Division of Urology. The study will be introduced to prospective patients seen by the investigator and coinvestigators. Routine standard of care surgery will be performed, and enrollment in the trial will not alter the surgery planned to be performed. The study will be available to the public, and the details of the inclusion criteria, exclusion criteria, and study design will be posted at [www.clinicaltrials.gov](http://www.clinicaltrials.gov).

Potential research subjects will be identified by a member of the patient's treatment team, the protocol investigator, or research team at MSKCC. If the investigator is a member of the treatment team, s/he will screen their patient's medical records for suitable research study participants and discuss the study and their potential for enrolling in the research study. Potential subjects contacted by their treating physician will be referred to the investigator/research staff of the study. If the potential participant has not already consented

to MSKs biospecimen study, 06-107 or 12-245 they will be approached and consented for both studies concurrently.

The principal investigator may also screen the medical records of patients scheduled to undergo radical prostatectomy with whom he does not have a treatment relationship for the limited purpose of identifying patients who would be eligible to enroll in the study and to record appropriate contact information in order to approach these patients regarding the possibility of enrolling in the study.

During the initial conversation between the investigator/research staff and the patient, the patient may be asked to provide certain health information that is necessary to the recruitment and enrollment process. The investigator/research staff may also review portions of their medical records at MSKCC in order to further assess eligibility. They will use the information provided by the patient and/or medical record to confirm that the patient is eligible and to contact the patient regarding study enrollment. If the patient turns out to be ineligible for the research study, the research staff will destroy all information collected on the patient during the initial conversation and medical records review, except for any information that must be maintained for screening log purposes.

In most cases, the initial contact with the prospective subject will be conducted either by the treatment team, investigator, or the research staff working in consultation with the treatment team. The recruitment process outlined presents no more than minimal risk to the privacy of the patients who are screened, and minimal PHI will be maintained as part of a screening log. For these reasons, we seek a (partial) limited waiver of authorization for the purposes of (1) reviewing medical records to identify potential research subjects and to obtain information relevant to the enrollment process; (2) conversing with patients regarding possible enrollment; (3) handling of PHI contained within those records and provided by the potential subjects; and (4) maintaining information in a screening log of patients approached (if applicable).

Patients will be screened on the basis of disease type and surgery status. Informed consent will be obtained before surgery. Candidate patients will be allowed time to consider the study, read the informed consent document at their convenience, and discuss it with family and others, as desired. Once the patient is ready to provide informed consent, this will occur in-person, with the subject providing written informed consent. Obtaining consent over the phone is not permitted.

**Estimated accrual:** On the basis of clinical volumes of similar cases and previous clinical trials conducted at MSK, the estimated accrual is 2 to 4 patients per month overall. We anticipate accrual of the potential maximum of 50 patients will take less than 18 months.

## 7.2 Randomization

Not applicable.

## **8.0 INFORMED CONSENT PROCEDURES**

Before protocol-specified procedures are carried out, consenting professionals will explain full details of the protocol and study procedures as well as the risks involved to participants prior to their inclusion in the study. Participants will also be informed that they are free to withdraw from the study at any time. All participants must sign an IRB/PB-approved consent form indicating their consent to participate. This consent form meets the requirements of the Code of Federal Regulations and the Institutional Review Board/Privacy Board of this Center. The consent form will include the following:

1. The nature and objectives, potential risks and benefits of the intended study.
2. The length of study and the likely follow-up required.
3. Alternatives to the proposed study. (This will include available standard and investigational therapies. In addition, patients will be offered an option of supportive care for therapeutic studies.)
4. The name of the investigator(s) responsible for the protocol.
5. The right of the participant to accept or refuse study interventions/interactions and to withdraw from participation at any time.

Before any protocol-specific procedures can be carried out, the consenting professional will fully explain the aspects of patient privacy concerning research specific information. In addition to signing the IRB Informed Consent, all patients must agree to the Research Authorization component of the informed consent form.

Each participant and consenting professional will sign the consent form. The participant must receive a copy of the signed informed consent form.

## **9.0 PRE-TREATMENT/INTERVENTION**

This protocol includes all pretreatment evaluations currently included in the clinical care standards for patients undergoing surgery at MSK. These include:

- Routine history and physical examination, to include documentation of any comorbidities, medications (including complementary and alternative medications), surgical history, family history, social history (alcohol and tobacco use), height, body weight, and Karnofsky performance status within 30 days of surgery
- Multiparametric prostate MRI before surgery
- Preoperative laboratory investigations: complete blood cell count, basic chemistry panel, urinalysis, and urine culture if indicated within 30 days of surgery

Patients will undergo baseline assessments of cognitive and neurologic function by use of the following validated instruments: the Beijers questionnaire for CTC grading of peripheral neuropathy (Appendix B) and the Neuropathy Impairment Scale–Lower Limbs (Appendix A). These same validated instruments will be used at the postoperative time points listed above;

if a change from baseline is identified, a full neurologic assessment will be performed to determine whether the change is considered to be related to the drug.

## **10.0 TREATMENT/INTERVENTION PLAN**

1. The operating team will consist of surgeons on faculty in the MSK Department of Surgery in the Division of Urology. The appropriate lines and monitors will be placed by the anesthesiology team and general anesthesia will be induced. Invasive monitoring will be at the discretion of the anesthesia team.
2. The procedures will be performed with the patient under general anesthesia in accordance with standard procedures. Intravenous fluid use during surgery will be provided by the anesthesiology team as clinically indicated. Hypovolemic resuscitation will be avoided. The total volume of fluids provided (typically 2000-2500cc of crystalloids during the case), as well as estimated blood loss, will be recorded.
3. The patient will receive a single intravenous dose of Illuminare-1 over 5 min at the assigned dose level approximately 30 minutes before anticipated real-time need for intraoperative nerve visualization, which corresponds to the start time of the pelvic lymph node dissection portion of the surgery. The precise timing of administration of Illuminare-1 will be at the discretion of the operating surgeon, according to the procedure being performed.
4. In the preoperative area, Holter monitors will be placed on patients for 24-hour research ECG data collection. We plan on ECG extractions at the following timepoints:
  - a. 3 baseline timepoints preoperatively
  - b. 0.25, 0.5, 2, 4, 8, 12, 24 hours postdose to align with the PK timepoints

For these ECG extractions, the patient will be supine in a comfortable resting position for ~10 minutes, the first 5 minutes to allow the heart rate and autonomic tone to stabilize, and the second 5 minutes for the ECG 'extraction window'. Exact timepoints will be recorded.

5. Blood will be drawn at baseline, 15, 30, 120, 240, 480 minutes (all +/- 10min), 12 hours (+/- 1h), 18 hours (+/- 2h), and 24 hours (+/- 2h) after injection for pharmacokinetics evaluation in all patients. In addition, a minimum of 3 patients in each dose cohort will also have blood drawn at 48 hours (+/- 24h) and 72 hours (+/- 24h) after administration for pharmacokinetics evaluation. Blood draws for PK evaluation will be done after the ECG extraction window.
6. Surgery will be performed in accordance with current standards of care at MSK. No additional laparoscopic trocars other than those routinely used will be required. The standard 10mm laparoscope with the attached fluorescent camera system will be placed through the assistant port during the brief portions of the case when visualization under blue-light and white-light conditions is needed. The surgical approach will be at the discretion of the surgeon. None of

the techniques used during the surgery are considered to be experimental and all are considered standard therapeutic options for patients undergoing radical prostatectomy.

7. The duration of the surgical procedure will vary depending on the type of approach and the patient's clinical characteristics. The duration of the surgical procedure will be noted and images and videos will be captured.
8. Assessment of Illuminare-1 fluorescence will be assessed as described in section 4.2.

All tissue harvesting will be performed under the supervision of pathology faculty. For ethical reasons, the protocol does not authorize the excision of additional fluorescent deposits detected *in vivo* outside of the planned resection regions by use of the fluorescent camera system. However, excision of such tissues may be performed at the discretion of the operating surgeon if he/she deems it clinically necessary, safe, and in compliance with current standards of care to do so.

9. The entire intraoperative procedure will be video recorded with the collection of both conventional and fluorescent images and will be archived according to institutional guidelines. Videos will be used for *post hoc* collection of fluorescence imaging data (to avoid interrupting the surgical procedure).
10. It is estimated that visualization of the pertinent anatomy using the fluorescent camera system for the purposes of this study will add no more than 15 min to the total operative time. The actual time necessary for fluorescent imaging will be recorded as part of the study.
11. Patients exposed to a photosensitizing agent may experience a phototoxic skin reaction, such as a sunburn, when exposed to excessive ultraviolet light or phototoxic drugs. As a precaution and because the half-life of the agent is approximately 4 hours, we will avoid administration of phototoxic drugs such as St. John's wort, griseofulvin, thiazide diuretics, sulfonylureas, phenothiazines, sulphonamides, quinolones, and tetracyclines for 24 hours before and after administration of Illuminare-1. These medications are uncommonly administered during the standard preoperative and postoperative pathway for patients undergoing minimally invasive radical prostatectomy.
12. Patients will be evaluated prior to discharge on postoperative day 1 and repeat neurologic examinations performed at baseline will be performed. Patient will also receive a CTN telephone call within 2 days of surgery for toxicity evaluation.
13. Patients will be evaluated at the postoperative visit on POD 10 (+/- 5). Repeat neurologic examinations performed at baseline will be performed. One tube of blood will be drawn for future research purposes under MSK IRB#06-107 or MSK IRB#12-245.

14. Patients will be evaluated at a postoperative visit on POD 30 (+/- 5) with a telephone follow-up. Patients are not routinely seen between the day 10 visit and the first PSA lab assessment so a telephone visit to assess for toxicity will be performed and if necessary, an in-person visit will be coordinated if there is clinical concern.
15. Patients will be evaluated at the postoperative visit on POD 45(+/- 10) corresponding to the first PSA blood level assessment. Repeat neurologic examinations performed at baseline will be performed. One tube of blood will be drawn for future research purposes under MSK IRB#06-107 or MSK IRB #12-245.

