event after administration of the agent occurs, the clinical signs, symptoms, laboratory assessments, and other observations will be recorded. The adverse event will be assessed by the primary investigator to determine if the adverse event was caused by administration of the agent (see section 15 for definitions of causality). The intensity of an adverse event will be graded according to the NCI Common Toxicity Criteria v 5.0. Adverse events that cannot be graded using the NCI Common Toxicity Criteria will be graded as mild (asymptomatic), moderate (symptomatic but not interfering significantly with function) or severe (causing significant interference with function). The pharmacokinetics of Illuminare-1 will be evaluated. Dose levels of the agent will be administered starting at 0.25mg/kg, with increases in dose between cohorts of no more than 0.5 mg/kg until a maximum dose of 2.25mg/kg is reached, if needed. At the dose identified to have the acceptable NMR and no associated DLTs, Illuminare-1 will be studied in up to 20 additional patients at this dose to optimize the imaging protocol and provide additional safety data. Blood samples will be drawn at days 10 ( $\pm$  5 days) and 45 ( $\pm$  10 days) and stored for potential future research investigations under MSK IRB#06-107 or MSK IRB#12-245. Neurologic assessments, using the Neuropathy Impairment Scale – Lower Limbs and Beijers questionnaire for CTC Grading of Peripheral Neuropathy, will be performed at enrollment (baseline assessment), during hospitalization after surgery, and at the routinely scheduled postoperative visits at days 10 ( $\pm$  5 days) and 45 ( $\pm$  10 days). A phone follow-up will be made at 30  $\pm$  5 days. Video of the white-light and blue-light assessments of the nerves of interest will be recorded throughout the procedure and provided to the investigators and company sponsor for *post hoc* analysis for future hardware and software optimization. Twenty four hour ECGs will be collected via Holter monitor and stored for *post hoc* analysis.

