| Urine culture (if indicated)                                | X |   |   |   |   |   |   |
| ECG                                                         | X |   | X |   |   |   |   |
| Research ECG via 24-hour Holter monitor †                   |   | X | X |   |   |   |   |
| Adverse events** CTCAE 5.0                                  |   |   | X |   | X | X | X |
| Neurologic assessment                                       | X |   | X |   | X |   | X |
| Subjective fluorescence assessment of obturator nerve       |   | X |   |   |   |   |   |
| Subjective fluorescence assessment of neurovascular bundles |   | X |   |   |   |   |   |
| Blood sampling for pharmacokinetics ***                     |   | X | X | X |   |   |   |
| PSA lab assessment*                                         |   |   |   |   |   |   | X |
| Blood for future research purposes (under 06-107 or 12-245) |   |   |   |   | X |   | X |
| Ex vivo tissue H&E                                          |   |   | X |   |   |   |   |
| Video evaluation (duration of surgery, NMR)                 |   | X |   |   |   |   |   |

\*Standard of care evaluations.

\*\*Serious adverse events will be reported from the time of informed consent to the end of study evaluation (45 +/- 10 days). Adverse events considered to be related to the drug that are grade ≥2 will be reported from the time of Illuminare-1 administration to the end of study evaluation. Adverse events from the time of informed consent to Illuminare-1 administration will be recorded in the medical history. Postsurgery (<24 hr) AE evaluation will occur via a CTN phone call within 2 days of surgery.

\*\*\*Blood will be drawn at baseline, 15, 30, 120, 240, 480 minutes (all +/- 10min), 12 hours (+/- 1h), 18 hours (+/- 2h), and 24 hours (+/- 2h) after injection for pharmacokinetics evaluation in all patients. In addition, a minimum of 3 patients in each dose cohort will also have blood drawn at 48 hours (+/- 24h) and 72 hours (+/- 24h) after administration for pharmacokinetics evaluation.

† ECG extraction timepoints: 3 baseline timepoints preoperatively; 0.25, 0.5, 2, 4, 8, 12 and 24 hours post-dose to align with PK timepoints. Patients to be comfortably resting in a supine position for ~10 minutes, the first 5 minutes to allow the heart rate and autonomic tone to stabilize, and the second 5 minutes for the ECG 'extraction window'. Exact timepoints will be recorded.

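### The stated 24-hour Holter recording is too short to hold both the preoperative baselines and the 24-hour post-dose ECG extraction

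*Protocol*

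**What the plan says.** Section 10.0, item 4 fixes where the recorder goes on and how long the collection is: in the preoperative area, "Holter monitors will be placed on patients for 24-hour research ECG data collection". It then lists the extractions. Before dosing there are "3 baseline timepoints preoperatively". After dosing they fall at "0.25, 0.5, 2, 4, 8, 12, 24 hours postdose to align with the PK timepoints". For each one, "the patient will be supine in a comfortable resting position for ~10 minutes": five minutes to settle, then a five-minute extraction window.

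Item 3 of the same section puts the single dose "approximately 30 minutes before anticipated real-time need for intraoperative nerve visualization", which the protocol equates with the start of the pelvic lymph node dissection. The surgeon chooses the exact moment.

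The 24-hour length is repeated elsewhere. Section 4.1 says "Twenty four hour ECGs will be collected via Holter monitor and stored for" post hoc analysis. Section 4.2 (Part 1, item 7) repeats the 24-hour length and the post hoc purpose. The Section 11.0 schedule has a row "Research ECG via 24-hour Holter monitor", and its footnote gives the same extraction times as Section 10.0.

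The readable text does not say when recording starts or stops, whether the 24 hours count from placement or from injection, or what time window an ECG extraction is allowed.

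**The concern.** The recording length and the extraction list are both explicit, and they do not fit together. The recorder has to be running for the baselines, which come before the dose, and still be running 24 hours after the dose. A 24-hour recording cannot span both.

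The extraction most exposed is the last one. It is paired with the 24-hour PK sample, which is the last sample drawn in every patient; the 48- and 72-hour draws are required only in a minimum of three patients per dose cohort. In a first-in-human study with safety as a primary objective, it is the planned Holter point closest to washout. An ECG that was not recorded cannot be recovered later.

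**Working it through.** This is timeline arithmetic.

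**Inputs from the protocol**
- Recording length: 24 h (Sections 4.1, 4.2, 10.0, 11.0).
- Baselines: three, all preoperative (Sections 10.0 and 11.0).
- Post-dose extractions: 0.25, 0.5, 2, 4, 8, 12 and 24 h (Sections 10.0 and 11.0).
- One extraction: about 10 min, of which the last 5 min are the extraction window (Section 10.0).
- Window on the 24-hour PK draw: ±2 h (Section 10.0, item 5). None is stated for the ECG.

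**Assumption.** Let L be the time from the start of recording to the dose. The protocol does not give it. L is above zero because the baselines precede the dose. I show 0.5 to 4 h. The lower value corresponds to three separate 10-minute baselines (3 × 10 min = 0.5 h) with nothing further before dosing.

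**Formulas**
- Required recording length = L + 24 h, plus up to 5 min for the last window.
- Last recorded time after dose, if recording stops 24 h after it starts = 24 h − L.

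| L (assumed) | Required length, before the extra 5 min | Recording ends, after dose | Last nominal extraction covered |
|---|---|---|---|
| 0.5 h | 24.5 h | 23.5 h | 12 h |
| 1 h | 25 h | 23 h | 12 h |
| 2 h | 26 h | 22 h | 12 h |
| 4 h | 28 h | 20 h | 12 h |

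The stated 24 h is therefore not reproduced as sufficient for any L above zero.

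**Counting the 24 h from the dose instead.** The recording then just reaches the 24-hour point, but the three baselines lie before it begins. The conflict moves to the other end of the recording.

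**Borrowing the PK window.** If the ECG may move with its paired blood draw, it can be taken from 22 h after dose. A 5-minute window fits when 22 h + 5 min ≤ 24 h − L, that is, when L ≤ 1 h 55 min. With a longer lead it no longer fits.

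**What the 24-hour point adds over the 12-hour point.** The nonclinical section gives terminal half-lives of 4 to 6 h in rats and dogs. Assume the same range and simple first-order decline in humans. The fraction remaining is 0.5 raised to (time ÷ half-life):
- At 12 h: 0.5^3 = 12.5% (4 h half-life) to 0.5^2 = 25% (6 h).
- At 24 h: 0.5^6 = 1.6% to 0.5^4 = 6.3%.

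**The case against.** The best answer is that 24-hour is only a label for the type of monitor, and that the extraction list is the operative instruction. Staff working from the list would leave the recorder on until the last extraction, and the patient is still there: Section 11.0 keeps patients in hospital for 24 h after administration, and Section 15.0 says approximately 24 hours. The timeline figure in Section 10.0 is not visible in the text available and may show start and stop times.

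A reader might infer that the 24-hour ECG is lost in every patient. The protocol does not support that. The inference needs recording to start at placement, to stop at exactly 24 h, and to have no tolerance on the extraction time, and the text states none of the three. With the PK window borrowed, an ECG at 22 h or later survives for leads up to about 1 h 55 min.

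A reader might also infer that no other late ECG exists, or that a safety decision depends on this one. Section 11.0 has a separate ECG row ticked before surgery and within 24 h after it. The Holter data are kept for post hoc analysis, and no dose-limiting toxicity definition, escalation rule or stopping criterion names them.

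These points limit the consequence but do not remove the conflict. The length is stated in four sections and matches the extraction list under neither way of counting. The PK window is attached to the blood draw, and with dose timing left to the surgeon, relying on it would let the point survive in some patients and not in others. The separate ECG has no stated time after dose, rest period or PK pairing, so it is not a like-for-like substitute.

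**Conclusion.** The point holds as a conflict between two stated specifications. The extraction schedule needs 24 h plus the lead from first baseline to dose, about 24.5 to 28 h for an assumed lead of 0.5 to 4 h, and the protocol states 24 h. That the length is too short needs only the fact that the baselines precede the dose; the size of the shortfall rests on the assumed lead.

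The consequence is conditional. If recording stops 24 h after placement, the nominal 24-hour ECG is at risk, and 12 h is the last Holter extraction that is assured. The other six post-dose extractions are covered at every lead shown. No stated trial decision changes, so this is worth correcting but does not threaten the trial's conclusions.

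**What to change.** In Section 10.0, item 4, define the recording by its end points: it runs from before the first baseline extraction until the 24-hour post-dose extraction window is complete. Use the same wording in Section 4.1, Section 4.2 (Part 1, item 7) and the Section 11.0 row and footnote, and check the timeline figure in Section 10.0 against it. Stating a time window for the ECG extractions in the same sentence would settle whether they may move with the paired PK draw.

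The cost is one sentence and its repeats, and a recorder worn somewhat longer than 24 h by patients who are already due to stay in hospital about 24 h after dosing. Deleting the 24-hour extraction from Sections 10.0 and 11.0 would also restore consistency, but it gives up the planned ECG closest to washout.

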## **Part 1**

1. Surgery with patients under anesthesia is anticipated to have a duration of 4-6h and will be conducted per routine.
2. An arterial line will be placed to monitor vital signs and allow for sequential blood draws throughout the case. Arterial lines are placed in select patients undergoing prostatectomy, but this is not standard for all cases. Patients will be informed that this monitoring will be additional to the standard anesthesia anticipated for such cases and will be reviewed in the informed consent document.
3. Blood will be drawn at baseline and at 15, 30, 120, 240, 480 minutes ( $\pm$  10 min), 12 hours ( $\pm$  1h), 18 hours ( $\pm$  2h), and 24 hours ( $\pm$  2h) after administration for

pharmacokinetics analysis in all patients. In addition, a minimum of 3 patients in each dose cohort will also have blood drawn at 48 hours (+/- 24h) and 72 hours (+/- 24h) after administration for pharmacokinetics analysis.

4. The obturator nerve will be used as the reference nerve, and intensity of fluorescence will be recorded. The obturator was selected as the reference nerve for the following reasons: it is a nerve structure universally encountered during all pelvic lymph node dissections, owing to its anatomically consistent location; fat, vasculature, lymphatics, and muscle structures are adjacent and can serve as background tissues for fluorescent intensity comparisons; it is a myelinated structure that would be anticipated to fluoresce after administration of Illuminare-1 in humans; and it has fluoresced in all animal models used to date when assessed. Fluorescence will be graded on a 5-point scale.

Intensity of Fluorescence Subjective Scale:

1 = no fluorescence of obturator nerve

2 = no difference in contrast between background enhancement and reference nerve

3 = minimal contrast between obturator nerve fluorescence and background normal tissues

4 = moderate contrast between obturator nerve fluorescence and background normal tissues

5 = maximal contrast between obturator nerve fluorescence and background normal tissues

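### All designated Holter ECG baselines are preoperative, but the ECGs nearest peak exposure fall under general anaesthesia; add a pre-dose window after induction as their baseline

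*Protocol*

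**What the plan says.** Section 10.0, item 4, starts the recording before surgery: "In the preoperative area, Holter monitors will be placed on patients for 24-hour research ECG data collection". It designates "3 baseline timepoints preoperatively" as the baselines and lists post-dose extractions at "0.25, 0.5, 2, 4, 8, 12, 24 hours postdose to align with the PK timepoints". The condition that follows is general: "For these ECG extractions, the patient will be supine in a comfortable resting position for ~10 minutes", with the first half of that time for heart rate and autonomic tone to settle and the second half as the extraction window. The footnote to the schedule in Section 11.0 repeats the plan: "3 baseline timepoints preoperatively; 0.25, 0.5, 2, 4, 8, 12 and 24 hours post-dose to align with PK timepoints".

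The same section says of the operation: "The procedures will be performed with the patient under general anesthesia in accordance with standard procedures". The dose is given over 5 min, about 30 minutes before nerve visualisation is expected to be needed, "which corresponds to the start time of the pelvic lymph node dissection portion of the surgery". The exact time is left to the surgeon. Section 4.2, Part 1, item 1, adds: "Surgery with patients under anesthesia is anticipated to have a duration of 4-6h and will be conducted per routine".

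Section 3.0 b) says that plasma concentration is highest straight after dosing and falls fairly fast over the first 2 hours. Section 4.1 describes a single-arm study and says that the Holter ECGs are stored for post hoc analysis. No section defines an ECG baseline between induction and dosing.

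**The concern.** The ECG times are matched to the PK samples, and each blood draw follows its ECG window, so the plan evidently means to relate ECG findings to concentration. The resting condition shows that the authors also wanted each ECG taken in a comparable state. The schedule does not deliver that. The baselines are taken before anaesthesia, while the ECGs at the highest concentrations are taken during anaesthesia and surgery.

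These are the first human Holter data for this agent. If heart rate or an ECG interval shifts at 0.25 to 2 h, comparison with the designated baseline cannot show how much is due to the drug and how much to anaesthesia, positioning, blood loss or other intraoperative drugs. A real effect could be put down to anaesthesia, or an anaesthetic effect charged to the drug. There is no untreated group to settle the matter.

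**Working it through.** The plan states no sample size, power or analysis model for the ECG data, so there is no figure to reproduce. The check is one of timing, followed by what the remaining comparisons can offer.

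**1. Which extractions fall under anaesthesia.** An ECG at t hours after the dose is under anaesthesia if

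(induction-to-dose interval) + t < (duration of surgery).

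Duration is 4 to 6 h (Section 4.2, Part 1), counted here from induction. The induction-to-dose interval is not stated; 0.25 to 2.5 h is assumed.

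| Surgery | Dose after induction | 0.25 h | 0.5 h | 2 h | 4 h | 8, 12, 24 h |
|---|---|---|---|---|---|---|
| 4 h | 0.25-1.5 h | under | under | under | after | after |
| 4 h | 2-2.5 h | under | under | after | after | after |
| 6 h | 0.25-1.5 h | under | under | under | under | after |
| 6 h | 2-2.5 h | under | under | under | after | after |

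So 2 of the 7 post-dose extractions are intraoperative throughout. The 2 h one is too, unless surgery is short and dosing late (4 h surgery, dose 2 h or more after induction). The 4 h one is intraoperative only with 6 h surgery and a dose less than 2 h after induction.

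The response definition in Section 4.2 agrees on the 2 h point. Grading starts at 30 minutes and grade 4 must last 90 minutes, so a patient counted as a responder is still being viewed at about 30 + 90 = 120 minutes. That is a condition for response, not a minimum operating time.

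**2. What change from baseline estimates.** Write A for the shift caused by anaesthesia and surgery and D for the drug effect. Against the preoperative baseline, an intraoperative ECG estimates A + D, and no group in the design supplies A. Against a pre-dose window taken after induction, it estimates D plus only the change in anaesthetic and surgical conditions since that window.

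**3. What the later ECGs offer.** The first extraction that is after surgery in every scenario is at 8 h. With a mono-exponential fall, concentration relative to 0.25 h is 2^(-(t - 0.25)/half-life). At t = 8 h:

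- half-life 4 h (the value used in Section 4.2): 2^(-7.75/4) = 0.26
- half-life 6 h (upper end of the animal range in Section 3.0 b): 2^(-7.75/6) = 0.41

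Section 3.0 b) describes a faster early decline than this, so the true share is probably lower.

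**4. What contrasts between doses offer.** All dose levels share the operative setting, so A roughly cancels between cohorts. The difference detectable with 80% power at two-sided 5% is (1.96 + 0.84) x sqrt(2/n) standard deviations:

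- n = 5 per dose: 2.80 x 0.632 = about 1.8 SD
- n = 10 per dose: 2.80 x 0.447 = about 1.25 SD

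Only a large effect would show.

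**5. The resting condition.** It is written for all listed extractions with no exception. At 0.25 and 0.5 h the patient is anaesthetised and being operated on, so the condition cannot be met as written.

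**The case against.** The strongest reply is that the Holter ECGs are stored for post hoc analysis. They are no listed objective, do not appear in Section 14.0 and feed no escalation rule. No section says that the analysis will be change from the preoperative baseline. The recording runs continuously, so someone could read a pre-dose intraoperative window later. Clinical safety does not rest on the Holter alone: Section 11.0 schedules a separate ECG before surgery and within 24 h after it, and Section 15.1.1 has clinically significant ECG abnormalities recorded as adverse events.

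Most of this stands and limits the weight of the point. It does not remove it. The protocol itself names the baselines and the extraction conditions, so this is a stated choice and not a detail left to an analysis plan. A baseline chosen after the data are seen is weaker than one fixed beforehand, and anaesthetic state and position are reliably available only if someone is told to record them.

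Three stronger readings go too far:

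- A reader might infer that at least three of the seven post-dose ECGs are intraoperative in every patient. The unstated induction-to-dose interval and the surgeon's discretion over timing do not allow that; only two are so in all scenarios.
- A reader might infer that no drug effect on the ECG could be assessed at all. The 8 to 24 h ECGs and the contrasts between doses carry some information, though little.
- A reader might infer that the Holter already holds a usable pre-dose baseline. That depends on enough time between induction and injection, which no section guarantees.

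**Conclusion.** The point holds in a limited form. The designated baselines do not match the state of the patient at the 0.25 and 0.5 h extractions, usually not at 2 h, and at 4 h only in longer operations with early dosing. Near peak exposure, change from the designated baseline is drug effect plus anaesthesia and surgery, with nothing in the single-arm design to separate them. The resting condition also conflicts with the timing of these same extractions.

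This rests on the stated 4-6 h duration, on an assumed interval of 0.25 to 2.5 h from induction to dose, and on reading preoperative as awake, which the text implies but does not say. The 26-41% figure further assumes mono-exponential decline and half-lives of 4 to 6 h.

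It would be wrong to read this as a flaw in the primary safety endpoint or the dose rules, since the Holter data enter neither. It is an inexpensive improvement to the interpretability of safety data that are being collected anyway.

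**What to change.** In Section 10.0, item 4, and in the ECG footnote to Section 11.0:

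- Add at least one pre-dose extraction window from the same Holter recording, after induction and positioning and shortly before injection. Add more if the interval to the dose allows.
- Name this window as the baseline for extractions made under anaesthesia, and keep the preoperative baseline for those made after recovery.
- Limit the supine resting condition to extractions in awake patients.
- Record anaesthetic state and position at each intraoperative extraction, including the new baseline.

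The Holter is already on the patient, so there is no added patient procedure. The cost is a few more windows to read and a short intraoperative record. The change does not remove drift in anaesthesia, blood loss or other intraoperative drugs after the dose, and any report of the early ECGs should say so.
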